### Study population

The trial will enroll patients from our outpatient clinic of hereditary ataxias at the AOU Federico II University. Our outpatient clinic currently follows 120 patients with molecular diagnosis of FRDA with regular bi-annual visits. An additional number of patients attend the center on a less regular basis. Patients' clinical and molecular data are stored in an electronic database that will be used for pre-screening purposes. We will enroll patients based on prescreening procedures, i.e., already known patients, through enrollment calls via the Italian association for Ataxia (AISA).

During our last phase II trial with EPO, we managed to recruit 46 patients in a 24-week interval (Saccà et al., 2016). For that study, inclusion/exclusion criteria were more stringent as patients were required to be able to perform a cardiopulmonary exercise test with an arm ergometer. We were able to include patients with a SARA score up to 32 and have them perform the CPET. Based on the inclusion/exclusion criteria of this trial, we will be able to complete enrollment during a 24-week interval.

Based on inclusion criteria, and in a similar way to the previous trial (Saccà et al., 2016), we will include patients with an age equal to or higher than 12 years. The reason for dosing minors is that FRDA does affect teenagers and children. This group is considered as a whole; exclusion of minors would lead to biased results and exclude patients who would benefit more from an innovative treatment. In addition, the use of DMF in minors does not require any additional test, nor did it raise any additional side effects as compared to adults. In the present study, it will be up to the physician's discretion to exclude patients not able to perform CPET from the trial.

The study will have specific withdrawal criteria linked to the safety of DMF treatment that can be found in Table 1. This will be an abnormal laboratory result showing abnormalities in any of the following: lymphocyte count (<0.5/L), neutrophils (<0.5/L), AST (>5 × UNL), or ALT (>5 × UNL). In addition to these specific criteria, the treating physician will be free to exclude patients with any adverse event or laboratory results that he/she considers life threatening or that could interfere with the study. In the case of withdrawal, patients will be monitored with laboratory exams and clinical visits as needed until resolution of the abnormality. Throughout the trial, and starting from a pre-specified time before screening in parenthesis, patients will not be allowed on the following drugs: DMF (180 days), Idebenone and other coenzyme Q10 analogs (30 days), Nicotinamide (90 days), Nicotinic acid (90 days), Valproic acid (30 days), Interferon-gamma (90 days), Erythropoietin (180 days), Etravirine (180 days), or any experimental drugs (180 days). The rationale for prohibited medications is the demonstrated *in-vitro* or *in-vivo* ability to increase FXN/mRNA or frataxin levels.

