After oral intake, DMF is rapidly hydrolyzed by esterases to its active circulating metabolite monomethyl fumarate (MMF). DMF is currently administered due to its lower incidence of gastrointestinal side effects compared to MMF (Litjens et al., 2004). MMF's bioavailability is decreased by concurrent food ingestion, though it remains bioavailable. MMF is the most bioactive metabolite (Litjens et al., 2004) and typically reaches peak serum concentrations around 20 μM. MMF is eliminated mainly through breathing; only small amounts of intact MMF are excreted through urine or feces. There is no evidence for a cytochrome P450-dependent metabolism in the liver, thus few drug interactions would be expected. MMF's half-life *in vivo* is around 12 h. The safety profile of DMF (trade name: Skilarence) is well-known and adverse events of special interest that have been considered for Skilarence are (EMA/412737/2017, 2017) leukocytopenia and lymphopenia, flushing, gastrointestinal disorders, hepatic injury, malignancies, renal injuries and proteinuria, and serious and opportunistic infections. The reported incidence of leukocytopenia is 13.3%, and lymphopenia is 10.0%, with very few patients (<1%) experiencing severe enough lymphopenia (<0.5/L) to lead to discontinuation. Flushing has an incidence of up to 20.8% of patients, is more frequent during the first weeks of treatment, and tends to resolve during long-term administration of DMF. Gastrointestinal disorders were reported in 62.7% of patients receiving DMF. They usually resolved after the first few months of treatment. The proportion of patients with an increase in hepatic enzymes is 7.5% and all are usually mild/moderate intensity. There is no evidence that long-term treatment with DMF is associated with an increased risk of malignancies. The proportion of patients reporting renal injury/proteinuria is low (<3%). Several of these cases of renal toxicity occurred with doses of fumaric acid esters that are much higher than the dose recommended for DMF in psoriasis/MS. In all of these cases, the renal function returned to normal after stopping treatment. The number of infections during DMF treatment was very low (<5%). All infections resolved by the end of the studies or during the 2-month follow-up period. No relation was found between leukopenia/lymphopenia and infections.

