**Figure 2 F2:**
[figure not shown]
Study visit plan and procedures. V1, visit 1; V2, visit 2; V3, visit 3; V4, visit 4; V5, visit 5; V6, visit 6; V7, visit 7; V8, visit 8; V9, visit 9; V10, visit 10; ECG, electrocardiogram; Con Meds, concomitant medications; SARA, Scale for the Rating and Assessment of Ataxia; m-FARS, modified Friedreich Ataxia Rating Scale; FXN/mRNA, *FXN* gene mRNA measurement; PRT, PATA rate test; 9HPT, 9 hole pegboard test; ADL/IADL, activities of daily living/Instrumental activities of daily living; EQ-5D, European quality of life scale; CPET, cardiopulmonary exercise test; EcoCG, echocardiography.

The use of placebo is based on several factors. On one side, there is a need for a more accurate evaluation on the biochemical effect on FXN/mRNA and frataxin that can show fluctuations over time. For this reason, an increase of FXN/mRNA in an open-label trial could be erroneously attributed to treatment. The second reason is that secondary endpoints (CPET, Clinical scales, etc.) can show a clear placebo effect once patients take part in a clinical trial. There is no known risk of being in the placebo group as there is no treatment available for FRDA.

The study will begin with a screening visit where patients will sign their informed consent (Figure 2). We will then assess inclusion and exclusion criteria (Table 1). Patients fulfilling all inclusion and none of the exclusion criteria will undergo endpoint measurement and will enter the core phase of the study.

**Table 1 T1:** Inclusion and exclusion criteria.

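### The lymphocyte and neutrophil withdrawal limits are printed as <0.5/L, without the multiplier (evidently 10^9) that would make them usable

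*Protocol article*

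**What the plan says.** The Study population section introduces safety-related withdrawal criteria and then lists four laboratory triggers. Two are blood counts: "lymphocyte count (<0.5/L), neutrophils (<0.5/L" per litre. The other two are liver enzymes: "AST (>5 × UNL), or ALT (>5 × UNL". The same section adds discretion for the investigator: "the treating physician will be free to exclude patients with any adverse event or laboratory results that he/she considers life threatening", or results that could interfere with the study.

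The section on dimethyl fumarate (DMF) uses the same lymphocyte figure in describing the known safety profile: "with very few patients (<1%) experiencing severe enough lymphopenia (<0.5/L) to lead to discontinuation". That section also lists leukocytopenia and lymphopenia among the adverse events of special interest.

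The reader is told that the trial has "specific withdrawal criteria linked to the safety of DMF treatment that can be found in Table 1". Table 1 is the eligibility table and lists only "inclusion and exclusion criteria".

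**The concern.** Blood counts are very large numbers per litre, so a limit of 0.5 per litre needs a multiplier to mean anything. Without one, the only laboratory result below the limit is zero. A patient with severe lymphopenia or neutropenia would not meet the criterion if it were followed to the letter.

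The limit is a decision rule in the methods. It determines when a patient, who may be as young as 12, stops a drug known to lower lymphocyte counts. It also affects who remains in the analysis, because the Statistical analysis section makes the analysis per protocol. Such a limit should be usable as printed, without the reader having to supply the unit.

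**Working it through.** **Inputs**

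- Printed limit for lymphocytes and for neutrophils: <0.5/L (Study population).
- Same figure for lymphopenia leading to discontinuation, reached by <1% of patients (section on DMF).
- Lymphopenia of any degree: 10.0% (section on DMF).
- Patients exposed to DMF: 20 in the core phase and 40 over both phases (Statistical analysis).
- Circulating blood volume: 4 to 6 L. This is an assumption; the article gives no figure.

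**Literal reading.** At 0.5 cells per litre, the whole circulation would hold 0.5 × 4 = 2 to 0.5 × 6 = 3 lymphocytes. One cell per µL is 10^6 cells per litre, already 10^6 / 0.5 = 2 million times the printed limit. No non-zero count can meet the criterion.

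**Comparison with the drug section.** That section says a small fraction of treated patients, under 1%, reach this figure and stop. The literal value and that statement cannot both be true. They agree only if a large multiplier has been left out.

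**Reading with the multiplier.** With the usual count unit, 0.5 × 10^9 cells/L ÷ 10^6 µL/L = 500 cells/µL. This fits the description of severe lymphopenia. The ratio to the printed value is (0.5 × 10^9) / 0.5 = 10^9. The article never prints 10^9, so this value is inferred from the conventional unit and from the drug section.

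**Does anything else in the article supply the unit?** No. Table 1, where the reader is sent, holds eligibility criteria only. No other section gives a count unit, and for neutrophils no other value appears at all.

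**How often the corrected rule might apply.** This takes the cited rates to hold over 12 to 24 weeks of treatment.

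| | Core-phase DMF arm (20) | All DMF-exposed (40) |
|---|---|---|
| Below the lymphocyte limit, at the 1% upper bound | 0.01 × 20 = 0.2 | 0.01 × 40 = 0.4 |
| Chance of at least one such patient | 1 − 0.99^20 = 0.182 | 1 − 0.99^40 = 0.331 |
| Any lymphopenia, at 10.0% | 0.10 × 20 = 2 | 0.10 × 40 = 4 |

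The first two rows are upper bounds, since the cited rate is below 1%. The last row shows how many patients might have a low count to compare with the limit. The table shows how often the limit would matter, not the harm from the misprint. The article gives no rate for neutrophils below the limit, so none is computed.

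**The case against.** The strongest reply is that nobody would be misled. Half a cell per litre is absurd, the drug section makes the intention clear, and any clinician would read 0.5 × 10^9/L. Table 2 schedules haematology at every visit, the physician may withdraw patients at discretion, and withdrawn patients are followed until the abnormality resolves. The article is also a condensed publication; site staff work from the full protocol, which may print the unit correctly. On this view it is an editorial slip, and the expected counts above do not measure any consequence of it.

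Much of this stands. The practical risk is low, the counts are only context, and the correct unit may well be in the full protocol. Two things remain. The article states the limits and states them wrongly, which is different from leaving detail to a fuller document. And the discretion clause supplements the fixed limits without defining them.

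A second reply is that the multiplier may have been lost when the article was converted to text. That cannot be fully excluded, but it is unlikely. The multiplication sign survives in the same sentence for AST and ALT, exponents survive in the left-ventricular mass formula under Echocardiography, and the Greek letter in μM survives in the drug section. A look at the published page settles it.

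The wrong reference to Table 1 carries little weight by itself, because the criteria follow in the next sentence.

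**Conclusion.** The concern holds. Two of the four laboratory withdrawal limits are wrong as printed and cannot operate if followed literally. The evident intention is <0.5 × 10^9/L for both, a factor of 10^9 from the text. The AST and ALT limits are unaffected.

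The consequence is small. At the cited rate, fewer than 0.2 lymphocyte withdrawals are expected in the core-phase DMF arm and fewer than 0.4 among all DMF-exposed patients, so the effect on the analysis set is negligible. Sample size, power and alpha do not change. The conclusion rests on the multiplier being absent from the article itself and, for the corrected value, on 10^9/L being the intended unit. It is worth correcting because it is a numerical safety limit and the correction costs almost nothing.

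**What to change.** In the Study population section, print both blood-count limits as <0.5 × 10^9/L (500 cells/µL), after confirming the value against the full protocol. Make the lymphopenia figure in the section on DMF match. Either remove the reference to Table 1 for the withdrawal criteria or add the criteria to that table.

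The cost is a unit correction in two sentences and one cross-reference. Visits, sample size and analyses stay as they are.

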### Endpoints

#### Primary endpoints

The primary objective of the study is to evaluate the effect of DMF compared to placebo on *FXN* gene expression level considering the change from baseline to 12 weeks (core phase of the DMF-FA-201 study).

#### Secondary endpoints

The secondary clinical objectives are to examine changes on the cardiopulmonary exercise outputs (VO_2_max, anaerobic threshold, and peak workload) and echocardiographic measures; and to evaluate differences in the Scale for the Rating and assessment of Ataxia (SARA), modified Friedreich Ataxia Rating Scale (m-FARS), 9-hole pegboard test (9HPT), EQ-5D, Activities of Daily Living (ADL)/Instrumental Activities of Daily Living Scale (IADL), and number and distribution of serious and non-serious adverse events between DMF and placebo.

The secondary laboratory objectives are to determine the effect of DMF on *FXN* and frataxin protein considering the change from baseline to week 12 and week 24 and at week 1 of the core phase, and at week 1 of the extension phase for those patients transitioning from placebo to DMF, compared to other time-points obtained after a DMF dose of 240 mg BID. Other secondary endpoints explore the effect of DMF on Nrf2 pathway genes (*NFE2L2, NQO1, HMOX1, PDLIM1*, and *NCF2*), on mitochondrial biogenesis genes (mt-ND6, mtCYB, mt-CO_2_, and mt-ATP6), and on mtDNA/nDNA.

### Clinical measures

An independent rater, blinded to laboratory results and side effects, will measure clinical endpoints (SARA and 9HPT). This will be necessary in order to assure that clinical measures will not be influenced by the treating physician in the case they accidentally recognize treatment allocation, based on side effects or laboratory results. EQ-5D and ADL/IADL will be self-rated. FXN/mRNA and frataxin protein are recognized endpoints for phase II clinical trials in FRDA patients (Libri et al., 2014). The investigation of the Nrf2 pathway and mitochondrial biogenesis genes are the logical consequence of DMF's mechanism of action and should be closely monitored during a clinical trial.

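### The independent blinded rater is assigned only SARA and 9HPT, so m-FARS and, less strongly, the PATA rate test lack the protection the plan calls necessary

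*Protocol article*

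**What the plan says.** The Clinical measures section assigns assessors in three steps.

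- It names a protected assessor and lists that person's tasks: "An independent rater, blinded to laboratory results and side effects, will measure clinical endpoints (SARA and 9HPT").
- It gives the reason: "This will be necessary in order to assure that clinical measures will not be influenced by the treating physician". The situation it has in mind is a physician who works out the patient's arm by accident, from adverse effects or from laboratory findings.
- It assigns the remaining questionnaires to the patient: "EQ-5D and ADL/IADL will be self-rated".

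The Secondary endpoints section lists m-FARS beside the protected 9HPT among the outcomes to be compared between DMF and placebo: "modified Friedreich Ataxia Rating Scale (m-FARS), 9-hole pegboard test (9HPT), EQ-5D". The section describing the scales presents m-FARS as a 0 to 85 examination covering bulbar function, limb coordination and upright stability. The PATA rate test has its own section as a 10-second speech task done twice and averaged. The Statistical analysis section includes it (as PRT) among the measures analysed like the other secondary endpoints. No section names an assessor for m-FARS or the PATA rate test.

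**The concern.** The stated reason for independent rating covers clinical measures in general, but the list of protected measures has two entries. Nothing in the article explains why SARA needs protection and m-FARS does not. Both are examiner-scored ataxia scales, described under one heading and scheduled at the same visits.

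The route to unblinding is the plan's own: side effects and laboratory results. The drug section reports that "Gastrointestinal disorders were reported in 62.7% of patients receiving DMF", and gives flushing in up to 20.8%. Haematology is run at every visit. The Trial design section also argues for a placebo group partly because secondary endpoints such as the clinical scales can show a placebo effect, so the plan itself treats these scales as open to expectation.

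At stake is the credibility of one named secondary endpoint, and to a lesser degree of one further test. If m-FARS and SARA disagreed at week 12, nobody could tell whether the drug or the difference in rating conditions was responsible.

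**Working it through.** The plan gives no figure on this point to reproduce. The check matches each clinical scale and timed test to its assessor and its visits.

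| Measure | Assessor in Clinical measures | Visits in Table 2 |
|---|---|---|
| SARA | Independent blinded rater | Screening, baseline, week 12, week 24, study interruption |
| m-FARS | None named | Screening, baseline, week 12, week 24, study interruption |
| 9HPT | Independent blinded rater | Baseline, week 12, week 24, study interruption |
| PATA rate test | None named | Baseline, week 12, week 24, study interruption |
| EQ-5D | Patient | Baseline, week 12, week 24, study interruption |
| ADL/IADL | Patient | Baseline, week 12, week 24, study interruption |

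Three things follow.

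1. m-FARS has exactly the visits of SARA, and the PATA rate test exactly those of 9HPT. At each visit where an unassigned measure is due, the independent rater is already scoring a protected one.
2. m-FARS is the clearer gap: it is a scored examination and a named secondary endpoint. The PATA rate test is a repetition count over a fixed interval and is missing from the Secondary endpoints list. However, the plan protects 9HPT, also a timed performance test, so its own logic reaches the PATA test.
3. The comparison that matters is week 12. From week 14 all patients take the full DMF regimen, and the Statistical analysis section makes the analysis that adds extension-phase patients descriptive.

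How many patients might give a cue, as context only: with 20 patients per arm and the rates in the drug section, the DMF arm would have about 20 × 0.627 = 12.5 patients with gastrointestinal disorders and up to 20 × 0.208 = 4.2 with flushing. These rates come from other uses of DMF. The article gives no placebo rates and no estimate of how far a rater who guessed allocation would shift a score. A bias estimate needs both, so none is offered.

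**The case against.** Several points can be made for the plan.

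- **The trial is double-blind.** Only accidental recognition is at issue. True, but the independent rater was introduced for exactly that situation.
- **The parenthesis may simply be incomplete.** The purpose sentence speaks of clinical measures generally, and lists drift elsewhere: the Statistical analysis section omits m-FARS from its named scales, and the Secondary endpoints section omits the PATA test. A condensed article may leave assessors to the full protocol. This reading is plausible. Yet the article does not leave the matter open. It states who rates what, and the statement needs correcting even if the gap is one of drafting.
- **Cues may have faded by week 12.** The drug section says that gastrointestinal disorders usually resolve after the first few months and that flushing is more frequent in the first weeks. This weakens the cue at the key visit without removing it, since earlier events are known to the treating physician.
- **The stakes are limited.** The primary endpoint is a laboratory measure, and SARA, which the article calls the current European standard, is protected. Both stand, and they limit the importance of the point.

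Stronger readings are tempting and not supported. A reader might infer that the treating physician scores m-FARS; the article names nobody. A reader might infer that these two are the only clinical outcomes without a protected assessor. CPET and echocardiography, also secondary clinical outcomes, have no independent assessor named either, so the statement holds only among clinical scales and timed tests. A reader might also turn the 62.7% into an inflated false-positive rate. That would require an assumed placebo rate, an assumed size and direction of rater bias, and a decision on the planned Bonferroni correction, for which the article does not give the number of tests.

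**Conclusion.** The point holds as an inconsistency within the document. A safeguard described as necessary for clinical measures is fixed for SARA and 9HPT and, as written, does not reach m-FARS or the PATA rate test. The finding is firm for m-FARS and weaker for the PATA test. Bias is possible, not demonstrated, and its size cannot be derived from the article. The effect is confined to secondary clinical outcomes and leaves the qPCR primary endpoint and the sample size untouched. The conclusion assumes that the parenthesis means what it says; if the full protocol already assigns the rater to m-FARS and the PATA test, the article's sentence only needs to be brought into line. The change is worth making because it removes an avoidable source of doubt at little cost.

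**What to change.** Extend the sentence in Clinical measures so that the same independent rater, blinded to side effects and laboratory results, scores SARA, m-FARS, 9HPT and the PATA rate test at every visit where Table 2 schedules them. For m-FARS that means screening, baseline, week 12, week 24 and study interruption; for the PATA test it means baseline, week 12, week 24 and study interruption. While editing, align the lists: add the PATA test to Secondary endpoints and m-FARS to the scales named in Statistical analysis.

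The cost is some extra minutes per visit for a rater who is already scoring SARA or 9HPT at those visits. No extra visit is needed, and no extra staff provided that rater can also administer m-FARS, which the article does not address.

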#### The scale for the rating and assessment of ataxias and the modified Friedreich Ataxia Rating Scale

The SARA scale consists of eight items (gait, stance, sitting, speech disturbance, finger chase, nose-finger test, fast alternating hand movements, and heel-shin slide). The scale can score from 0 to 40, with 40 being the worst condition. The scale was validated in FRDA and is the current European standard for the measurement of ataxic symptoms over time (Bürk et al., 2009). It has been the standard for previous clinical trials (Saccà et al., 2016).

The m-FARS includes a bulbar, upper and lower limb coordination, and upright stability tests. The scale ranges from 0 to 85. It is a modified version of the original FARS and has been approved by the FDA as a clinical outcome for registration trials.

